### Secondary outcome

Secondary outcomes will include the average time of three 10-meter walk tests and assessments of gait and balance abilities. After subjects have completed the walk tests and sufficiently rested, gait and balance will be evaluated using the Tinetti Performance-Oriented Mobility Assessment (Tinetti POMA) (S5 Appendix). This comprehensive tool for assessing gait and balance in older adults was developed by Tinetti in 1986 and later modified by Cobbs et al. in 1999 [26]. The modified version of the Tinetti POMA scale includes a balance test with 9 items totaling 16 points and a gait test with 7 items totaling 12 points; the full scale reaches a maximum of 28 points, with higher scores indicating better balance and walking capabilities, and research has demonstrated that the Tinetti POMA scale possesses good reliability and validity [27]. Assessors receive standardized training prior to evaluations to ensure they can competently demonstrate and instruct each item according to the Tinetti POMA guidelines before conducting assessments.

### Statistical analysis

Statistical analysis will be conducted using SPSS 24.0 software, with graphical representations generated through Graph Pad Prism 8. Measurement data will be analyzed by the Kolmogorov-Smirnov test (K-S test), expressed as mean ± standard deviation (x̅ ± s) if they adhere to a normal distribution, with comparisons between groups made using the two independent samples t-test. For non-normally distributed data, results will be described using the median (interquartile range) [M(IQR)], and comparisons between groups will be conducted using the Mann-Whitney U test. Count data will be expressed as frequency (n) and constitutive ratio (%), with comparisons between groups performed using the χ^2^ test or Fisher’s exact test, and rank data comparisons utilizing the Wilcoxon rank-sum test. Effect sizes will be calculated using Cohen’s d value, and the significance level will be set at a two-sided *P *< 0.05.

The intraclass correlation coefficient (ICC) analysis, specifically the ICC(3,k) model, will be used to quantify the consistency and reproducibility of measurements. To assess the reliability of single measurements, the standard error of measurement (SEM) will be calculated using the formula SEM = SD/$\sqrt{n}$, where n represents the number of measurements per participant (i.e., 3). Additionally, the minimum detectable difference (MDD) will be calculated using the formula MDD = SEM × 1.96×$\sqrt{2}$ to determine whether observed differences exceed those expected from measurement error alone, at the 95% confidence level.

Associations between sEMG parameters and frailty status will initially be assessed using Pearson correlation analysis for normally distributed data or Spearman rank correlation analysis for non-normally distributed data. Subsequently, EMG parameters significantly associated with frailty status will be included in binary logistic regression models to further assess their predictive ability for frailty status, controlling for potential confounders such as age and gender. Finally, EMG parameters that prove significant in the logistic regression analysis will be evaluated for their sensitivity, specificity, and cutoff values for diagnosing frailty using receiver operating characteristic (ROC) curves.

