### Participants

Recruitment for the study will take place from November 2024 to April 2025 using non-randomized convenience sampling. Seventy-five older adults from the inpatient and outpatient departments of the Xiamen Cardiovascular Hospital of Xiamen University in China, who are assessed as frail using the Fried’s frailty phenotype [24], will be selected for the case group. An additional 75 non-frail older adults, matched by age, gender, and cultural background during the same period, will form the control group. All participants will sign an informed consent form (S3 Appendix) and undergo baseline assessments, which include comprehensive socio-demographic and clinical data collection, along with screening using the Fried’s frailty phenotype (S4 Appendix). A panel investigator will review the inclusion and exclusion criteria and assign participants to either the case or control group based on the Fried’s frailty phenotype screening results.

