### Selection criteria

#### Inclusion criteria.

(1)Case group1)Older individuals evaluated as frail using the Fried’s frailty phenotype [24], which includes five criteria: (i) Unintentional weight loss: a loss of more than 4.5 kg or more than 5% of body weight over the past year, excluding dieting and exercising. (ii) Slowed walking speed: time taken to walk 4.57 meters, assessed in conjunction with height and gender. (iii) Reduced grip strength: older adults are instructed to measure grip strength twice with their usual hand, and the average of these two measurements is evaluated against gender and body mass index (BMI). (iv) Decreased physical activity: measured using the Minnesota Leisure Time Activity questionnaire, with activity levels less than 383 kcal/week for men (approximately 2.5 hours of walking) and less than 270 kcal/week for women (about 2 hours of walking) indicating a reduction. (v) Self-reported fatigue: assessed using two questions from the Center for Epidemiological Studies-Depression (CES-D). Question 1: ‘I felt that everything I did was an effort during the past week.’ Question 2: ‘I could not get “going” during the past week.’ Scoring for questions 1 and 2 assigns 0 points for less than 1 day, 1 point for 1–2 days, 2 points for 3–4 days, and 3 points for more than 4 days, with a score of 2–3 points on any question indicating significant fatigue. One point is awarded for each criterion met, with a higher score indicating greater frailty. Scores of 3 or more indicate frailty, scores of 1–2 indicate pre-frailty, and a score of 0 indicates no frailty. 2) Age 60 years old and above. 3) Those who can walk independently without assistive devices. 4) Those who possess normal reading, understanding, and expressive abilities to engage in relevant assessments and tests. 5) Those who voluntarily participate in the study and sign the informed consent form.(2)Control group.

The control group will include older adults without frailty, with all other inclusion criteria identical to those of the case group.

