### Sample size calculation

The sample size calculation was performed using G*Power 3.1.9.7, based on an effect size of 0.433 derived from pilot study data. With a power of 80% and an alpha level of 0.05, the required sample size was calculated to be 67 subjects per group. Anticipating a 10% attrition rate, the sample size was adjusted to 75 subjects per group, resulting in a total of 150 subjects to ensure adequate power for detecting significant differences.

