**Fig 2 pone.0325356.g002:**
[figure not shown]
Figure of electrode placement and bandage fixation for surface electromyography recording.

(2)10-meter walk test: A 12-meter stretch will be marked on an open and flat 15-meter walkway, incorporating a 10-meter timed section flanked by 1-meter zones for acceleration and deceleration at both ends. After the surface EMG recording and reference electrodes have been properly placed, subjects will be instructed to stand still and relaxed at the starting line, with the aim of maintaining the EMG signal near the baseline (<10 μV) as displayed on the instrument. Upon the ‘start’ signal, participants will walk to the finish line at a comfortable pace, maintaining a natural walking speed. The time taken to traverse the 10-meter timed section will be recorded using a timer, and dynamic sEMG parameters of the lower limb muscles will be captured by the surface EMG device, complemented by recordings of different gait cycles using an infrared camera system for further analysis. Typically, three tests will be conducted with 1–2 minutes of rest between each, and the average result of these three tests will be calculated. The entire test will require the accompaniment of a researcher to ensure safety, without any physical contact, and no assistive devices will be used by the subjects during the test.

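### The group comparison ignores the matching factors, so it may be conservative and lose power, and with no speed-adjusted companion it cannot show whether sEMG differs beyond slower walking

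*Protocol article*

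**What the plan says.** The Abstract and Research design describe a category-matched case-control study with a 1:1 ratio. Participants says the controls are "matched by age, gender, and cultural background during the same period". Individual pairs are not described.

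For the between-group comparison, Statistical analysis describes normally distributed data "with comparisons between groups made using the two independent samples t-test" and uses the Mann-Whitney U test otherwise. No covariate enters either test. Adjustment appears only in the later logistic model for frailty status, "controlling for potential confounders such as age and gender". Quality control adds that confounders will be considered, without naming a variable or method.

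On speed, one of the five case-defining criteria is "Slowed walking speed: time taken to walk 4.57 meters, assessed in conjunction with height and gender". During the recording, "participants will walk to the finish line at a comfortable pace, maintaining a natural walking speed". Data processing takes the EMG from five gait cycles, and the IEMG formula sums rectified amplitude times the sampling interval over that window. The 10-meter time is listed as a secondary outcome and is named in no model.

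**The concern.** Matching makes the groups alike on age, gender and cultural background, so those factors contribute less to the chance difference between the group means. The independent-samples test still counts their contribution in its standard error. If they are related to sEMG, the interval is too wide and the test rejects less often than its nominal 5%. The study then pays for matching in recruitment and does not collect the gain in precision.

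The second matter concerns interpretation. Slow gait helps to define the cases, and everyone walks at their own pace. An unadjusted sEMG difference therefore combines any change in muscle activation with whatever follows from walking more slowly. The Introduction calls gait speed alone a less effective predictor, and the Discussion hopes for screening indicators and insight into mechanism. Both invite the question of what sEMG adds to speed, and no planned analysis answers it.

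**Working it through.** **Inputs from the article.** Standardised effect 0.433, 67 per group before attrition, 80% power and alpha 0.05 (Sample size calculation); two-sided 0.05 (Statistical analysis). **Assumed, because the article gives no figure:** R², the share of within-group sEMG variance explained by the matching factors; D, the speed gap in within-group SDs; r, the within-group correlation of sEMG with speed.

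**The plan's own figure.** An unmatched two-sample t-test with d = 0.433 and 80% power needs 67 per group at one-sided 0.05, which reproduces the plan; 67/0.9 gives 75. At two-sided 0.05 it needs 85. With 67 per group the two-sided test has 70.1% power, and this is the baseline below. The sidedness mismatch is a separate matter.

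**Matching factors.** If matching balances the factors, the group difference has standard error √(2/67) × √(1−R²) in SD units. The planned test uses √(2/67) = 0.173, too large by the factor 1/√(1−R²). With 0.433/0.173 = 2.506:

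- True size = 2[1 − Φ(1.96/√(1−R²))].
- Unadjusted power = Φ[(2.506 − 1.96)/√(1−R²)].
- Adjusted power: noncentral t with noncentrality 2.506/√(1−R²).

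| R² | SE too large by | True size | Unadjusted power | Adjusted power |
|---|---|---|---|---|
| 5% | 1.03 | 4.4% | 71% | 72% |
| 10% | 1.05 | 3.9% | 72% | 75% |
| 20% | 1.12 | 2.8% | 73% | 79% |
| 30% | 1.20 | 1.9% | 74% | 84% |

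The two power columns use slightly different approximations. With the normal approximation for both, the lower three rows read 71.8/72.9/74.3% against 75.2/80.0/85.0%. With t critical values for both they read 71.1/72.3/73.6% against 74.6/79.4/84.5%. Either way the gain is about 3.5, 7 and 11 points. At R² = 0 there is none.

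**IEMG and cycle duration.** By its formula IEMG is mean rectified amplitude times duration. Over a fixed five cycles, a cycle 10 to 30% longer (assumed) raises IEMG by 10 to 30% at the same mean amplitude. Normalising to EMG_max rescales amplitude and leaves duration unchanged. In the muscle contribution rate a common duration cancels.

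**Price of adjusting for speed.** With speed as a covariate, the variance of the group effect rises by the factor 1 + D²/4, offset in part by 1 − r². For a group difference of 0.433 at equal speed, the noncentrality is 0.433/√[(1−r²)(1+D²/4)(2/67)]. With r = 0.3:

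- D = 1.0: factor 1.25, SE 0.184, noncentrality 2.35, power about 65%.
- D = 1.5: factor 1.56, SE 0.206, noncentrality 2.10, power about 55%.
- D = 2.0: factor 2.00, SE 0.233, noncentrality 1.86, power about 45%.

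**The case against.** Several points on the other side stand.

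- Category matching most naturally means frequency matching, for which an independent-samples test is an ordinary choice. A reader might infer that a paired test or conditional logistic regression is required, but the article describes no individual pairs.
- Ignoring the matching factors is conservative and creates no false positives. The size of the loss rests on an assumed R², and normalisation to EMG_max may reduce the share that age and gender explain.
- A reader might infer that the logistic model leaves out cultural background. The wording there is an open list, so that factor is unnamed, not barred.

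On speed, a reader might infer that cases are slower by construction and that a significant result could be produced by speed alone. The article does not support going that far. Three of the five criteria suffice, so a case can qualify without slow gait. The induced difference would be r × D. It is 0.45 at r = 0.3 and D = 1.5, close to the planned 0.433, but only 0.2 at r = 0.2 and D = 1.0, and the article gives neither quantity. Nor is a difference that travels through slow gait spurious: the primary objective is to characterise sEMG in frail against non-frail adults, and the unadjusted contrast does that. The authors also suggest that muscle change underlies slow gait, so conditioning on speed may remove part of the effect of interest. These points rule out a speed-adjusted model as the main analysis. They do not remove the case for showing it alongside.

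**Conclusion.** The point holds in two limited parts.

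First, the article fixes a matched design and then fixes group tests that ignore the matching factors. The consequence is lost precision, not bias toward a positive finding: about 3.5 to 11 points of power for an assumed R² of 10 to 30%, and next to nothing if R² is near 0. This assumes that matching balances the three factors well.

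Second, the unadjusted contrast is a valid description, but it cannot tell whether sEMG differs beyond slower walking. For IEMG the dependence on cycle duration follows from the formula. For the other parameters the size is unknown, because the article gives neither the speed gap nor the sEMG-speed correlation. The plan is worth changing on both parts, but neither invalidates the comparison.

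**What to change.** 1. Make the main estimate a linear regression of each continuous sEMG parameter on group, age, gender and cultural background, and report the adjusted group difference with its 95% interval.
2. Name the same three factors as covariates in the logistic model.
3. Prespecify a companion regression that adds 10-meter walking speed (10 m divided by the recorded time). Report it beside the main estimate, not in its place. State that it may over-adjust, because speed is part of frailty and may lie downstream of muscle change, and that it is less precise. Show how far the groups overlap in speed, since little overlap makes the adjusted difference hard to interpret.

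The cost is analysis wording only: the matching factors and the walking time are already collected. The companion model's price is precision, with the variance of the group effect multiplied by 1.25 to 2.0 for a speed gap of 1.0 to 2.0 SD. It should not be presented as powered for 0.433.

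### ICC(3,k) alone supports consistency of the three-walk mean but not its reproducibility, and gives no coefficient for a single walk

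*Protocol article*

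**What the plan says.** All statements are in the protocol article.

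- **Statistical analysis** fixes the coefficient and its purpose: "specifically the ICC(3,k) model, will be used to quantify the consistency and reproducibility of measurements". No other ICC is named.
- The next sentence of that section turns to single walks, with a different statistic: "To assess the reliability of single measurements, the standard error of measurement (SEM) will be calculated using the formula" SD/√n, "where n represents the number of measurements per participant (i.e., 3").
- **Test program, (2) 10-meter walk test** gives the repeats: "three tests will be conducted with 1–2 minutes of rest between each", after which "the average result of these three tests will be calculated".
- **Secondary outcome** confirms that the mean is the unit analysed for walk time: "Secondary outcomes will include the average time of three 10-meter walk tests".

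The article gives no ICC value, no threshold for acceptable reliability and no data on change between walks.

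**The concern.** The sentence claims two properties, and the coefficient addresses one of them. Consistency asks whether participants keep their relative positions from walk to walk. Reproducibility, in the ordinary sense, asks whether the same value comes back. ICC(3,k) treats the three walks as fixed conditions and removes their mean differences before it is computed. If everyone changed by the same amount between walks, through practice or tiring, it would not move.

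The plan also sets out "To assess the reliability of single measurements", but the only ICC it names describes a mean of three.

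What is at stake is the reliability result as reported. If there is drift, a coefficient labelled as reproducibility would be higher than the agreement actually achieved. A reader interested in one walk would have no ICC to use. This bears somewhat on the diagnostic cutoffs planned from the ROC curves, because a fixed cutoff is applied to absolute values.

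**Working it through.** The plan states no reliability figure, so there is nothing of its own to reproduce. The check is what ICC(3,k) can and cannot register.

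**Inputs**
- k = 3 walks per participant (Statistical analysis; Test program).
- Single-walk ICC(3,1) = r: not given. Assumed 0.60, with a range of 0.30 to 0.90.
- Drift: not given. Assumed linear, with a total of 0, 0.5 or 1.0 SD from walk 1 to walk 3 (0, 0.25 or 0.5 SD per walk). The SD is that of one walk, so between-person variance is r, residual variance is 1 − r, and they sum to 1.

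**Why drift drops out.** With MSR, MSC and MSE the mean squares for participants, walks and residual, and n participants:
- ICC(3,k) = (MSR − MSE)/MSR. The walk term MSC does not appear.
- ICC(A,k) = (MSR − MSE)/(MSR + (MSC − MSE)/n). Here it does.

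An extreme case: three participants with walks (10, 12, 14), (20, 22, 24) and (30, 32, 34) give MSE = 0 and ICC(3,k) = 1.00, although every walk differs from the one before.

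**Formulas in variance terms**, with J the variance of the walk means:
- ICC(3,3) = 3r/(1 + 2r)
- ICC(A,3) = r/(r + (J + 1 − r)/3)
- ICC(A,1) = r/(1 + J)

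For steps of 0, 0.25 and 0.5 SD per walk, J = 0, 0.0625 and 0.25.

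**At r = 0.60**
- ICC(3,3) = 1.8/2.2 = 0.818, whatever the drift.
- ICC(A,3): 0.6/(0.6 + 0.4/3) = 0.818; 0.6/(0.6 + 0.4625/3) = 0.796; 0.6/(0.6 + 0.65/3) = 0.735.
- ICC(A,1): 0.6/1 = 0.600; 0.6/1.0625 = 0.565; 0.6/1.25 = 0.480.
- Gap for the mean, ICC(3,3) − ICC(A,3): 0, 0.02 and 0.08. (Subtracting the two-decimal values 0.82 and 0.73 gives 0.09; unrounded, 0.8182 − 0.7347 = 0.0835.)

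**Over the assumed range of r**

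| ICC(3,1) | ICC(3,3), any drift | ICC(A,3), total drift 0.5 / 1.0 SD | ICC(A,1), total drift 0.5 / 1.0 SD |
|---|---|---|---|
| 0.30 | 0.562 | 0.541 / 0.486 | 0.282 / 0.240 |
| 0.50 | 0.750 | 0.727 / 0.667 | 0.471 / 0.400 |
| 0.60 | 0.818 | 0.796 / 0.735 | 0.565 / 0.480 |
| 0.75 | 0.900 | 0.878 / 0.818 | 0.706 / 0.600 |
| 0.90 | 0.964 | 0.943 / 0.885 | 0.847 / 0.720 |

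The gap for the three-walk mean is about 0.02 at 0.5 SD and about 0.08 at 1.0 SD in every row.

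**Simulation check** (20,000 participants, r = 0.60): ICC(3,3) was 0.81, 0.82 and 0.82 at total drift 0, 1.0 and 2.0 SD, while ICC(A,3) was 0.81, 0.73 and 0.56. This agrees with the formulas.

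**The case against.** The case for leaving the plan as it is has real force.

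- **The averaged form fits the analysed quantity.** The mean of three walks is what enters the analysis, so a coefficient for a mean of three is correct. That 0.60 for one walk becomes 0.82 for three shows the benefit of averaging and is no overstatement. This stands.
- **The plan does not apply ICC(3,k) to a single walk.** A reader might infer that single-walk reliability will be inflated because the two sentences are adjacent. The text does not support that: single measurements are given to the SEM. Nor does an inflated ICC pass into the SEM or the minimum detectable difference, because the stated SEM formula contains no ICC. Whether that formula is sound is a separate question.
- **Drift is assumed.** Participants walk at a comfortable pace over a short course with 1–2 minutes of rest, and no drift is documented. Without drift the consistency and agreement forms coincide. ICC(3,k) is also blind only to a shift common to everyone; change that differs between people enters the residual and lowers it. This stands, and it makes the size conditional.
- **Pooling of groups is not stated.** A reader might infer that the case-control difference will be counted as between-person variance. The article does not say so. Even if it were, at the effect size of 0.433 used for the sample size the single-walk ICC would rise only from 0.60 to (0.60 + 0.433²/4)/(1 + 0.433²/4) = 0.62.
- **No decision depends on the ICC.** It selects no parameter for the tests, regression or ROC curves, and a shift common to both groups cancels in the group comparison. This stands.

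What the objection does not answer is that the plan specifies the coefficient and assigns it to reproducibility, a property it cannot measure. That is a stated choice, not a detail left out of a condensed article.

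**Conclusion.** The point holds as a minor one. As the only ICC, ICC(3,k) supports the stated consistency but not the stated reproducibility, and it gives no coefficient for a single walk.

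For the three-walk mean, the excess over absolute agreement is nil without drift, about 0.02 at a total drift of 0.5 SD and about 0.08 at 1.0 SD. These figures rest on assumed linear drift common to all participants, and they change little for single-walk ICCs from 0.30 to 0.90. The larger distance between ICC(3,3) and ICC(A,1) is mostly the effect of averaging and should not be read as bias.

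A general statement that the plan overstates the reliability of its measurements would go too far. The finding concerns how reliability is reported and, at most, how far a cutoff derived from the three-walk mean can be carried to other walks. The primary comparison of sEMG parameters between groups is unaffected.

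**What to change.** In the Statistical analysis section:

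1. Report the two-way absolute-agreement ICC(A,k), k = 3, for the three-walk mean, as the measure of reproducibility.
2. Report ICC(A,1) for single walks, so that the stated aim for single measurements has a matching coefficient.
3. Compute both within each group, so that the group difference does not enter the between-person variance.
4. Report the walk-order effect (mean of walks 1, 2 and 3 by group) beside them, so that any drift is visible.
5. Keep ICC(3,k) if wanted, labelled as consistency of the three-walk mean.

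The cost is small: the same three walks and the same software with a different ICC type, split by group. The coefficients will be somewhat lower if drift exists, the single-walk values will be lower in any case, and there will be a little more output to report.

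### The standard error of measurement for single measurements is given as SD/√3, with SD undefined and the ICC unused, so the reported SEM and MDD will not be the quantities named

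*Protocol article*

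**What the plan says.** The second paragraph of the protocol article's Statistical analysis section sets out a reliability analysis in three steps.

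- An intraclass correlation, "specifically the ICC(3,k) model, will be used to quantify the consistency and reproducibility of measurements".
- A standard error of measurement: "To assess the reliability of single measurements, the standard error of measurement (SEM) will be calculated using the formula SEM" = SD/√n, where n is the number of measurements on each participant and is set at 3. The text does not say which SD is meant.
- A threshold: "the minimum detectable difference (MDD) will be calculated using the formula MDD = SEM × 1.96" × √2, to be used "to determine whether observed differences exceed those expected from measurement error alone, at the 95% confidence level".

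The three measurements come from the 10-meter walk test, described under Test program: "three tests will be conducted with 1–2 minutes of rest between each, and the average result of these three tests will be calculated". No other part of the article gives a different SEM formula.

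**The concern.** The name and the stated purpose belong to one quantity and the formula to another. A standard error of measurement describes the scatter of one person's repeated readings about that person's true value. It is the square root of the error mean square, or equivalently the total SD times √(1 − ICC). Dividing an SD by the square root of the number of readings gives the standard error of a mean.

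The plan estimates an ICC but does not use it in the SEM, and it leaves open whether SD is taken across people or within a person. The MDD multiplier is standard, so the MDD is wrong only because it inherits the SEM. At stake are the published SEM and MDD for each sEMG parameter. The Discussion proposes these parameters as screening indicators for frailty, so others may reuse the values.

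**Working it through.** **Inputs.** From the Statistical analysis section: SEM = SD/√3 and MDD = 1.96 × √2 × SEM = 2.772 × SEM. From Test program: three walks, averaged. The article gives no numerical SEM or MDD, so there is no figure to reproduce. It gives no ICC either. I assume a single-measurement ICC between 0.5 and 0.95.

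**Reference quantity.** Let the variance of one measurement be between-person variance plus error variance, with ICC(3,1) the between-person share. Then single-measurement SEM = total SD × √(1 − ICC) = √MS_error, and MDD = 2.772 × SEM.

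**Reading A: SD is the total (observed-score) SD.** The plan gives SEM = 1/√3 = 0.577 SD and MDD = 0.577 × 2.772 = 1.60 SD at any ICC.

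| Assumed ICC | Correct SEM (SD) | Correct MDD (SD) | Planned MDD (SD) | Planned / correct |
|---|---|---|---|---|
| 0.5 | 0.707 | 1.96 | 1.60 | 0.82 |
| 0.667 | 0.577 | 1.60 | 1.60 | 1.00 |
| 0.8 | 0.447 | 1.24 | 1.60 | 1.29 |
| 0.9 | 0.316 | 0.88 | 1.60 | 1.83 |
| 0.95 | 0.224 | 0.62 | 1.60 | 2.58 |

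The two agree only where 1 − ICC = 1/3, that is at ICC 0.667. In a simulation of 200,000 participants with three trials each, pure test-retest differences exceeded the planned 95% limit in 10.8% of cases at ICC 0.5, 1.2% at 0.8 and 0.03% at 0.9. The nominal share is 5%, and the correct formula gave 5.0 to 5.1%.

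**Reading B: SD is the within-person SD over the three trials.** That SD is already the single-measurement SEM. Dividing by √3 = 1.73 gives the SEM of the three-trial mean. As a single-measurement figure it is too small by a factor of 1.73, or 42% (1 − 0.577 = 0.42). In the same simulation about 26% of single-measurement retest differences exceeded the resulting limit, instead of 5%.

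**MDD against a group difference.** The planning effect in Sample size calculation is 0.433. A correct single-measurement MDD falls below 0.433 SD only if 2.772 × √(1 − ICC) < 0.433, that is ICC > 1 − (0.433/2.772)² = 1 − 0.0244 = 0.976. By contrast, the uncertainty of a difference in group means shrinks with group size. With 67 per group, the half-width of its 95% confidence interval is about 1.96 × √(2/67) = 0.34 SD.

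**The case against.** The strongest reply is that n is defined per participant, which suits a within-person SD at least as well as a total SD. On that reading SD/√3 does vary with reliability. It is a valid SEM for the three-trial average, which is the value Test program says will be calculated, and it pairs naturally with ICC(3,k). This stands, and it means the choice of ICC(3,k) is not itself an error. It does not rescue the sentence, which names single measurements and leaves SD undefined.

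Three stronger readings are tempting, and the document does not support them.

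- A reader might infer that the planned MDD cannot separate reliable from unreliable parameters. That is true only on reading A.
- A reader might infer that the wrong formula would cause the planned group difference to be dismissed as measurement error. At each ICC in the table, the correct single-measurement MDD would dismiss 0.433 SD as well. That problem comes from setting a group difference against an individual-level limit, not from SD/√3. The article also does not tie 0.433 to any one parameter.
- A reader might infer that the MDD decides the primary result. It does not. Group comparisons rest on the t-test or Mann-Whitney test at two-sided P < 0.05, with Cohen's d. The MDD is an addition within the reliability paragraph, and no rule makes it a condition for the regression or ROC steps.

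Nor does the text say that the differences to be screened, "to determine whether observed differences exceed those expected from measurement error alone", are differences between groups. They could be differences between trials. The wording leaves both uses open and should be settled.

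**Conclusion.** The point holds as an error in the reliability analysis. Under neither reading does the stated formula define single-measurement error. On reading A it is a constant 0.577 SD that is right only by coincidence at ICC 0.667. The resulting MDD ranges from 18% too small at ICC 0.5 (ratio 0.82) to 2.58 times too large at ICC 0.95. On reading B the SEM and MDD are too small by a factor of 1.73. The direction of the error therefore depends on which SD is used and, on reading A, on the ICC. The ICC values are assumptions. The reading A figures apply to the total SD, not to a purely between-person (true-score) SD.

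The primary group tests, sample size, regression and ROC analyses do not use SEM or MDD and are unaffected. This should be fixed before SEM and MDD are reported, but it does not threaten the main comparison.

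**What to change.** Replace the SEM and MDD sentences with definitions at a stated level:

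- Single measurement: SEM = √MS_error from the two-way ANOVA of the three trials, equal to total SD × √(1 − ICC(3,1)).
- Analysed three-trial mean: SEM = √(MS_error/3), reported with ICC(3,k).
- MDD = 1.96 × √2 × the SEM of the same level.

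Add one sentence saying that the MDD applies to differences in an individual's values. Frail versus non-frail differences should be judged by their 95% confidence interval, because an individual-level MDD, even when correctly computed, is not a threshold for a difference in group means.

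The cost is two formula lines and one sentence. The three trials are already part of the test procedure, so no new data are needed.
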